# Desmopressin for reversal of Antiplatelet drugs in Stroke due to Haemorrhage (DASH): protocol for a phase II double-blind randomised controlled feasibility trial

**DOI:** 10.1136/bmjopen-2020-037555

**Published:** 2020-11-10

**Keywords:** stroke medicine, bleeding disorders & coagulopathies, anticoagulation, stroke, clinical trials

## Abstract

**Introduction:**

Intracerebral haemorrhage (ICH) can be devastating and is a common cause of death and disability worldwide. Pre-ICH antiplatelet drug use is associated with a 27% relative increase in 1 month case fatality compared with patients not using antithrombotic drugs. We aim to assess the feasibility of conducting a randomised controlled testing the safety and efficacy of desmopressin for patients with antiplatelet-associated ICH.

**Methods and analysis:**

We aim to include 50 patients within 24 hours of spontaneous ICH onset, associated with oral antiplatelet drug(s) use in at least the preceding 7 days. Patients will be randomised (1:1) to receive intravenous desmopressin 20 µg in 50 mL sodium chloride 0.9% infused over 20 min or matching placebo. We will mask participants, relatives and outcome assessors to treatment allocation. Feasibility outcomes include proportion of patients approached being randomised, number of patients receiving allocated treatment, rate of recruitment and adherence to treatment and follow-up. Secondary outcomes include change in ICH volume at 24 hours; hyponatraemia at 24 hours, length of hospital stay, discharge destination, early death less than 28 days, death or dependency at day 90, death up to day 90, serious adverse events (including thromboembolic events) up to day 90; disability (Barthel index, day 90), quality of life (EuroQol 5D (EQ-5D), day 90), cognition (telephone mini-mental state examination day 90) and health economic assessment (EQ-5D).

**Ethics and dissemination:**

The Desmopressin for reversal of Antiplatelet drugs in Stroke due to Haemorrhage (DASH) trial received ethical approval from the East Midlands—Nottingham 2 research ethics committee (18/EM/0184). The DASH trial is funded by National Institute for Health
and Care Research RfPB grant: PB-PG-0816-20011. Trial results will be published in a peer reviewed academic journal and disseminated through academic conferences and through patient stroke support groups. Reporting will be in compliance with Consolidated Standards of Reporting Trials recommendations.

**Trial registration numbers:**

NCT03696121; ISRCTN67038373; EudraCT 2018-001904-12.

Strengths and limitations of this studyThis is the first randomised controlled trial of desmopressin versus placebo for patients taking antiplatelet drugs with spontaneous intracerebral haemorrhage (ICH).Robust methodology developed from large international multicentre trials in spontaneous ICH such as TICH-2 and PATCH.Desmopressin and placebo are not identical so the person administering the intervention will not be masked to treatment allocation.All outcomes assessors are blinded to treatment allocation to minimise the risk of bias.This is the first randomised controlled trial of desmopressin versus placebo for patients taking antiplatelet drugs with spontaneous intracerebral haemorrhage (ICH).Robust methodology developed from large international multicentre trials in spontaneous ICH such as TICH-2 and PATCH.Desmopressin and placebo are not identical so the person administering the intervention will not be masked to treatment allocation.All outcomes assessors are blinded to treatment allocation to minimise the risk of bias.

## Introduction

### Haemorrhagic stroke

Spontaneous intracerebral haemorrhage (ICH) causes approximately 3 million deaths per year worldwide^1^ and is responsible for the loss of 64.5 million disability adjusted life years per year.^2^ Two-thirds of survivors are left dependent on others.^3^ Roughly one-third of patients are taking antiplatelet drugs at the time of ICH in high-income countries, and this proportion has been increasing over time.^4^ Pre-ICH antiplatelet drug use is associated with a 27% relative increase in 1 month case fatality compared with patients not using antithrombotic drugs.^5^ Despite development of effective treatments for ischaemic stroke (thrombolysis, thrombectomy, aspirin, hemicraniectomy) there is no proven effective drug treatment for ICH, although blood pressure lowering might improve outcome.^6^

### Haematoma expansion

Outcome after ICH is closely related to haematoma growth (expansion) which is associated with worse outcome (death and disability).^7^ Use of antiplatelet drugs or anticoagulants, time from onset of symptoms to baseline imaging, and ICH volume on baseline imaging are independent predictors of haematoma expansion.^8^

Platelet transfusion, tranexamic acid and recombinant activated factor VII have not been shown to improve outcomes after antiplatelet associated ICH, raising the need to consider alternatives.^9^

### Desmopressin

Desmopressin is a licensed pro-haemostatic drug that can be administered intravenously, subcutaneously, intranasally or orally and is used in a number of inherited bleeding conditions to treat or prevent bleeding.^10–12^ Platelet function remains inhibited for 5–7 days after stopping antiplatelet drugs. Desmopressin stimulates release of Von Willebrand Factor (VWF) and factor VIII from endothelial Weibel-Palade bodies. VWF is responsible for platelet adhesion to collagen and may also bind platelets through their glycoprotein IIb/IIIa receptors,^13^ so increased levels of VWF have the potential to compensate for the platelet function defect associated with antiplatelet drugs. Desmopressin may also increase the formation of procoagulant platelets.^14^

Desmopressin is recommended for the reversal of antiplatelet drugs in guidelines from the USA^15^ but not in UK guidelines.^16^ In a recent meta-analysis evaluating desmopressin for reversal of antiplatelet drugs for patients undergoing cardiac surgery, desmopressin was found to reduce blood loss, transfusion requirements and the need for a further operation due to bleeding.^17^

There are potential risks with use of desmopressin, including tachycardia hypotension, hyponatraemia and hyponatraemic seizures. A meta-analysis of 65 surgical randomised controlled trials, comparing desmopressin to placebo found no significant difference in rates of ischaemic stroke, myocardial infarction or venous thromboembolism.^18^

Desmopressin has been tested in ICH in four case series where it appears to be safe.^19–22^ However, the series were small, non-randomised and did not have a placebo control arm, so it is not possible to make a clear assessment of the benefits and harms of administering desmopressin for these patients. American neurocritical care guidelines for the treatment of intracranial haemorrhage recommend consideration of 0.4 μg/kg desmopressin for treatment of antiplatelet-associated ICH,^15^ although the level of evidence supporting this recommendation was recognised as very uncertain.

Searches of clinicaltrials.gov and WHO International Trials Clinical Registry Platform found no other ongoing randomised controlled trials of desmopressin vs placebo for reversal of antiplatelet drugs in stroke due to haemorrhage.

If it is feasible to recruit patients and to collect robust data then we intend to proceed to a definitive trial to test efficacy.

### Primary objective

To assess the feasibility of randomising, administering the intervention and completing follow-up for patients treated with desmopressin or placebo to inform a definitive trial.

## Methods and analysis

Desmopressin for reversal of Antiplatelet drugs in Stroke due to Haemorrhage (DASH) will be a multicentre double-blind randomised placebo-controlled, parallel group phase II feasibility trial. Participants will be enrolled by investigators from emergency departments or acute stroke units from 10 hospital sites in the UK. Patient flow though the trial is summarised in figure 1.

**Figure 1 F1:**
[figure not shown]
Study flowchart.

### Inclusion criteria

Adults (≥18 years).Confirmed ICH on imaging.Randomised less than 24 hours from onset of symptoms (or from when last seen free of stroke symptoms).Prescribed and thought to be taking a daily oral antiplatelet drug in the preceding 7 days (cyclo-oxygenase inhibitors, phosphodiesterase inhibitors or P2Y_12_ inhibitors).

### Exclusion criteria

Known secondary causes of ICH (aneurysmal subarachnoid haemorrhage or haemorrhage due to transformation of infarction, thrombolytic drug, venous thrombosis, arteriovenous malformation or tumour).Patients at risk of fluid retention.Systolic blood pressure less than 90 mm Hg.Known drug eluting stent in previous 3 months.Allergy to desmopressin.Pregnant or breast feeding.Life-expectancy less than 4 hours or planned for palliative care only.Glasgow coma scale less than 5.Modified Rankin scale (mRS) more than 4.

### Consent

Patients with capacity to give consent will be approached directly. If this is not possible, a relative or close friend will be approached for consent, if this is not possible then a professional not associated with the trial will be approached for proxy consent. Patients will be approached again for consent when they regain capacity (online supplemental files 1–3; all trial documents are available at: http://dash-1.ac.uk/docs/public.php).

10.1136/bmjopen-2020-037555.supp1Supplementary data

10.1136/bmjopen-2020-037555.supp2Supplementary data

10.1136/bmjopen-2020-037555.supp3Supplementary data

### Randomisation

Participants will be randomised centrally using a secure internet site in real-time. Treatment allocation will be concealed from all staff and patients involved in the trial. Randomisation involves minimisation on key prognostic risk factors: age (70 years or more); sex (male); time since onset (3 hours or more); systolic blood pressure (170 mm Hg or more); and presence (or no information on presence or absence) of intraventricular haemorrhage. This approach ensures concealment of allocation, minimises differences in key baseline prognostic variables and slightly improves statistical power.^23^ Randomisation will allocate a number corresponding to a treatment pack and the participant will receive treatment from the allocated numbered pack. It was considered not possible to mask/blind personnel preparing the injection for administration to the treatment allocation because the ampoules of active and placebo injections are different and carry the manufacturer’s identifying information. Clinicians, patients and outcome assessors (clinical, radiological and haematological assessors) will be blinded to treatment allocation.

In general, there should be no need to unblind the allocated treatment. If some contraindication to desmopressin develops after randomisation, the trial treatment should be stopped. Unblinding should be done only in those rare cases when the doctor believes that clinical management depends importantly on knowledge of whether the patient received desmopressin or placebo. In those few cases when urgent unblinding is considered necessary, the doctor will call an emergency telephone number. The caller will then be told whether the patient received desmopressin or placebo. The rate of unblinding will be monitored and audited.

### Intervention

Patients will be randomised to either 20 µg intravenous desmopressin (DDAVP, 4 µg/mL 1 mL glass ampoules, Ferring Pharmaceuticals) or placebo of intravenous sodium chloride 0.9%. Placebo was selected for comparison because at present there are no established haemostatic therapies for ICH. Either desmopressin 20 µg (5×4 µg/mL) will be added to 50 mL sodium chloride 0.9% and infused over 20 min, or three 2 mL sodium chloride 0.9% will be added to 50 mL sodium chloride 0.9% and infused over 20 min. The investigational medicinal product (IMP) will be stored between 2°C and 8°C until use. All patients will receive all usual standard care including venous thromboembolism prophylaxis with intermittent pneumatic compression devices, blood pressure lowering therapy and neurosurgery if appropriate.

We will administer a single dose as the risk of continued bleeding and haematoma expansion after ICH is greatest in the first few hours. High levels of factor VIII and VWF are maintained for 6–8 hours after intravenous infusion therefore we believe a repeated dose at 12–24 hours would not be indicated. This dose regime (0.4 μg/kg body weight administered by intravenous infusion) is recommended in American neurocritical care guidelines for the treatment of intracranial haemorrhage,^15^ although the level of evidence supporting this recommendation was recognised as very uncertain.

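### The fixed 20 µg dose is described as the guideline's 0.4 µg/kg regime, but the two agree only at 50 kg

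*Protocol article*

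**What the plan says.** The protocol article is consistent on what is given. The Abstract (Methods and analysis) specifies "intravenous desmopressin 20 µg in 50 mL sodium chloride 0.9% infused over 20 min or matching placebo". The Intervention section repeats it, "Patients will be randomised to either 20 µg intravenous desmopressin", and sets out one preparation for everyone: "Either desmopressin 20 µg (5×4 µg/mL) will be added to 50 mL sodium chloride 0.9% and infused over 20 min". It describes no adjustment for weight, no weight bands and no cap.

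The second paragraph of the Intervention section argues for a single administration. It closes by giving the regime, in a parenthesis, as 0.4 µg/kg and naming its source: "body weight administered by intravenous infusion) is recommended in American neurocritical care guidelines for the treatment of intracranial haemorrhage". The Introduction (Desmopressin) cites the same guidelines on the same per-kg scale; they "recommend consideration of 0.4 μg/kg desmopressin for treatment of antiplatelet-associated ICH". Both places add that the evidence behind the recommendation was regarded as very uncertain.

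The inclusion and exclusion criteria contain no weight limit. The Assessments section does not name weight among its baseline items, but it refers the reader to data collection forms that are not part of the article.

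**The concern.** In a section that describes only this trial's dosing, the subject of the guideline sentence is the trial's own regime, and the parenthesis gives that regime a per-kg value. The section has just fixed a total amount that does not depend on weight. Both descriptions cannot hold for participants of differing weight, and the article offers no reference weight or rounding rule to connect them.

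What is at stake is interpretation. The Outcomes section says that secondary data are collected to inform the design of a definitive trial. They include hyponatraemia at 24 hours and the change in factor VIII, VWF antigen and VWF activity at 1 hour. A reader who takes the guideline sentence at face value would attach those results to 0.4 µg/kg, when they belong to a fixed 20 µg whose per-kg value varies between participants.

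**Working it through.** **Inputs**

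- Trial dose D = 20 µg, fixed (Abstract; Intervention).
- Ampoules: 1 mL at 4 µg/mL, five per dose (Intervention).
- Regime cited: r = 0.4 µg/kg (Intervention; Introduction, Desmopressin).
- Body weight w: no distribution in the article, so the weights below are illustrative.

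**Step 1. The article's own dose.** 5 × 4 µg = 20 µg. The preparation reproduces the stated amount.

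**Step 2. Weight at which the two descriptions agree.** D/r = 20/0.4 = 50 kg.

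**Step 3. Dose per kg at other weights.** Dose per kg = 20/w; share of the cited figure = 20/(0.4w).

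| Weight (kg) | 20/w (µg/kg) | Share of 0.4 µg/kg |
|---|---|---|
| 45 | 0.44 | 111% |
| 50 | 0.40 | 100% |
| 60 | 0.33 | 83% |
| 70 | 0.29 | 71% |
| 80 | 0.25 | 62.5% |
| 100 | 0.20 | 50% |

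**Step 4. Could rounding explain it?** Suppose 0.4 is a rounded value standing for anything from 0.35 to 0.45. The matching weights then run from 20/0.45 = 44.4 kg to 20/0.35 = 57.1 kg. That is still a narrow band.

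**Step 5. How many participants might this touch?** This needs a weight distribution, which is assumed here: normal, mean 65 to 80 kg, SD 12 to 18 kg.

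- Share above 50 kg = 1 − Φ((50 − mean)/SD). The lowest value is at mean 65, SD 18: 1 − Φ(−0.83) = 0.798. The highest is at mean 80, SD 12: 1 − Φ(−2.50) = 0.994.
- Share outside 44.4 to 57.1 kg: from 0.785 (mean 65, SD 15) to 0.973 (mean 80, SD 12).

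Steps 1 to 4 use only the article's figures and arithmetic. Step 5 rests wholly on the assumed distribution.

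**The case against.** The strongest reply is that nobody can be misled about the dose: the fixed 20 µg opens the section, its preparation is spelled out, and the Abstract agrees. The guideline sentence closes an argument for giving a single dose, and the authors themselves call the supporting evidence very uncertain. An article also condenses a fuller protocol, which may explain the fixed amount.

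Much of this stands. The dose is unambiguous, and the absence of an explanation for a fixed dose is no finding against a condensed article. But the point here is something the article asserts. A fuller document could explain why 20 µg was chosen; it could not make 20 µg equal to 0.4 µg/kg at any weight other than 50 kg. If only the route or the single administration was meant, the sentence still attaches the wrong quantity to the regime.

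Four stronger readings are tempting, and the document does not support them:

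- *Weight is not recorded.* The baseline list in Assessments is not exhaustive. It also leaves out systolic blood pressure and time since onset, which are minimisation factors, and the Glasgow coma scale, which is an exclusion criterion. The forms are not shown.
- *The definitive trial would test the per-kg regime.* Nothing in the article says so. If that trial used the same fixed dose, these data would describe the dose to be used.
- *A weak factor VIII or VWF response could be put down to a lower dose per kg.* That presumes response scales with dose per kg, on which the article is silent.
- *The rationale is false for most adults.* That depends on assumed weights. It holds across the range tried in the working, but the document itself establishes only the 50 kg crossover.

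**Conclusion.** The statement that the trial's regime is the guideline's 0.4 µg/kg is wrong as written. The two agree at exactly 50 kg, and at about 44 to 57 kg if generous rounding is allowed. At 60 to 100 kg the fixed dose is 83% to 50% of the cited figure; at 45 kg it is 111%. The crossover needs no assumption; any statement about the share of participants affected does.

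The consequence is limited. This does not show that 20 µg is the wrong dose, and it leaves recruitment, treatment delivery, adherence and follow-up untouched. The article plans no formal efficacy assessment, so no test or power figure is affected. What changes is which regime the factor VIII, VWF and sodium data can be said to represent. That warrants correction because those data are collected to inform the next trial.

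**What to change.** 1. Reconcile the fixed 20 µg with the 0.4 µg/kg statements in the Intervention section and in the Introduction (Desmopressin). The sponsor should state how the two relate or give the actual basis for the trial dose. Which is right is for the sponsor's clinicians.
2. Do not describe the trial, in the protocol or in the results, as testing the per-kg guideline regime unless it does.
3. Confirm that measured or estimated body weight is captured on the forms, with a flag for which it is.
4. Report the achieved µg/kg in the desmopressin arm descriptively, beside the 1-hour factor VIII and VWF changes and the 24-hour sodium. This fits the descriptive analysis already planned.

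The cost is a wording correction, at most one baseline field with its flag, and one descriptive table. Some weights will be estimates, so the achieved dose per kg will carry error. With 50 participants randomised 1:1, the active arm has about 50/2 = 25, which is enough to describe the spread but not to support a dose-response conclusion.

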### Assessments

Participants’ age, sex, medical history, antiplatelet drug use, ICH location, intraventricular haemorrhage and mRS will be assessed at baseline by local investigators. Participants will be reviewed again on day 2, hospital discharge and on day 90 to gather information on interventions, adverse events, discharge date and discharge destination. Data collection forms can be found in online (https://dash-1.ac.uk/).

At day 90 central assessors trained in the appropriate questionnaires and masked to treatment allocation will follow-up each patient by telephone. Barthel index, mRS, EuroQOL, cognition (mini-mental state examination) and serious adverse events will be assessed by telephone.

Brain imaging (CT head) will be undertaken as part of routine care before enrolment. A second research CT head scan will be performed 24 hours after treatment with the IMP to measure parenchymal haematoma volume. Haematoma volume will be measured centrally by trained assessors masked to treatment allocation using semi-automated segmentation. We will assess change in haematoma volume at 24 hours, and proportion of patients with haematoma expansion, defined as an absolute increase of greater than 6 mL or relative growth of greater than 33%.

To assess baseline platelet function, platelets will be stimulated with arachidonic acid (which is inhibited by aspirin) or adenosine diphosphate (which is inhibited by P2Y12 inhibitors). Platelet cell surface P-selectin expression (a measure of platelet activation) will then be measured using a standardised assay (Heptinstall; patent pending (PTC/GB2008/050169)) to assess retrospectively whether patients were taking antiplatelet drugs, as previously described.^24^ VWF antigen, VWF activity and factor VIII (1-stage) will be measured centrally by assessors masked to treatment allocation. Blood samples will be drawn into 0.109M citrate and centrifuged at 2500g for 15 min. Platelet poor plasma will be aspirated and stored at −80°C at each site and then transferred to the central laboratory at the end of the trial for analysis. These tests will be performed for research only and the results will not be fed back to the clinical team. Serum sodium will be assessed locally 24 hours after administration of the IMP and these results will be available to the clinical team.

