### Outcomes

This is a feasibility trial and the primary outcomes are based around feasibility: number of eligible patients who receive allocated treatment; rate of eligible patients randomised; proportion of eligible patients approached; proportion of eligible patients randomised and reasons for non-randomisation; adherence to intervention; proportion of participants followed up to 90 days and reasons for loss to follow-up; proportion of randomised participants with full outcome data available, and reasons for non-availability.

Secondary outcomes data will be collected to inform the design of a definitive trial but will not be statistically analysed. Secondary outcomes are change in ICH volume at 24 hours; hyponatraemia at 24 hours, length of hospital stay, discharge destination, early mortality less than 28 days, death or dependency at day 90, mortality up to day 90, serious adverse events (including thromboembolic events) up to day 90; disability (Barthel index, day 90), quality of life (EuroQol, day 90), cognition (telephone mini-mental state examination day 90) and health economic assessment (EQ-5D). Baseline platelet dysfunction will be measured and correlated with response to desmopressin; and change in factor VIII, VWF antigen and VWF activity will be assessed 1 hour after administration of desmopressin.

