### Adverse events

All adverse events on day 1 (including during infusion) and for the 24 hours period post dose will be collected. All adverse events will be assessed for seriousness, expectedness and causality by adjudicators masked to treatment allocation. Serious adverse events will be categorised in accordance with the medical dictionary for regulatory authorities. As the IMP is administered once and has a short half-life, serious adverse events occurring within the first 7 days will be assessed for seriousness, expectedness and causality. In addition, fatal serious adverse events and safety outcome events (fluid overload, hyponatraemia) will be reported until day 90.

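### The 24-hour hyponatraemia rate mixes sodium that was already low before dosing with new cases; a pre-dose value with new-onset and change summaries would be a cheap improvement

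*Protocol article*

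**What the plan says.** All references are to the Protocol article.

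- **Named harm** (Introduction, Desmopressin): "There are potential risks with use of desmopressin, including tachycardia hypotension, hyponatraemia and hyponatraemic seizures".
- **Outcome** (Outcomes): "hyponatraemia at 24 hours". No threshold and no reference to an earlier value is given.
- **Measurement** (Assessments): "Serum sodium will be assessed locally 24 hours after administration of the IMP and these results will be available to the clinical team". No other sodium measurement is timed.
- **Baseline data** (Assessments): the list starts with age and sex and continues "medical history, antiplatelet drug use, ICH location, intraventricular haemorrhage and mRS will be assessed at baseline by local investigators". Sodium is not in it.
- **Entry and allocation** (Exclusion criteria; Randomisation): low sodium is neither an exclusion nor a minimisation factor. The nearest exclusion is risk of fluid retention, which states no sodium criterion.
- **Second reporting route** (Adverse events): "fatal serious adverse events and safety outcome events (fluid overload, hyponatraemia) will be reported until day 90", and "All adverse events will be assessed for seriousness, expectedness and causality by adjudicators masked to treatment allocation".
- **Other before-and-after measures** (Assessments; Outcomes): haematoma volume, factor VIII, VWF antigen and VWF activity are all to be assessed as change.
- **Analysis** (Statistical analysis): descriptive only, with safety data grouped by the treatment actually received.

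**The concern.** A patient whose sodium is low before the infusion and still low a day later counts as having the outcome, although the treatment did not cause the low value. Such patients can enter either arm. The recorded rate then answers how many patients have low sodium at 24 hours, when the useful safety question is how many developed it, or how far sodium fell, after dosing.

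Secondary outcomes are collected to inform a definitive trial. With no formal comparison planned, the raw rates by arm are what a reader or the Data Monitoring Committee will look at. If a sizeable part of a small event count was present before dosing, the rate overstates how often the drug produces the harm. The difference between arms also depends partly on how pre-existing cases happened to fall.

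**Working it through.** **No figure to reproduce.** The article gives no sodium prevalence, no hyponatraemia rate and no power calculation. What follows is an illustration, with assumptions marked.

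**Inputs**
- From the article: 50 patients randomised 1:1, so n = 25 per arm.
- Assumed: b, the share low before dosing and still low at 24 hours, is 0.05, 0.10 or 0.20.
- Assumed: new-onset rates among patients normal before dosing are i0 = 0.02 on placebo and i1 = 0.20 on desmopressin.

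**Step 1: dilution.** The status rate in an arm is b + (1 − b)·i. The difference between arms is therefore (1 − b)·(i1 − i0), which is the new-onset difference reduced by the fraction b. At b = 0.10:
- placebo: 0.10 + 0.90 × 0.02 = 11.8%
- desmopressin: 0.10 + 0.90 × 0.20 = 28.0%
- difference: 16.2 points, against 18 points for new onset.

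**Step 2: precision.** The SE is √[p0(1 − p0)/n + p1(1 − p1)/n]. For new onset, n is replaced by the expected number normal before dosing, 25(1 − b). At b = 0.10:
- status: √[(0.118 × 0.882 + 0.28 × 0.72)/25] = 11.1 points; difference/SE = 1.47
- new onset: √[(0.02 × 0.98 + 0.20 × 0.80)/22.5] = 8.9 points; difference/SE = 2.01.

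These ratios show signal against noise only; no test is proposed.

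**Step 3: composition and chance imbalance.** Expected pre-existing cases per arm are 25b. Their share of recorded desmopressin-arm events is b/[b + (1 − b)·i1]. The chance of a gap of 3 or more such patients between arms comes from two independent binomials (25, b).

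| | b = 0.05 | b = 0.10 | b = 0.20 |
|---|---|---|---|
| Pre-existing cases per arm | 1.25 | 2.5 | 5 |
| Status difference (points) | 17.1 | 16.2 | 14.4 |
| Difference/SE, status | 1.72 | 1.47 | 1.14 |
| Difference/SE, new onset | 2.07 | 2.01 | 1.90 |
| Pre-existing share of desmopressin-arm events | 21% | 36% | 56% |
| P(gap of 3 or more between arms) | 0.099 | 0.231 | 0.374 |

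These figures treat every patient counted as low before dosing as still low at 24 hours. If some recover, the last row overstates the imbalance that reaches the 24-hour count, so its values are upper ones for each admission prevalence.

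**Step 4: change in sodium.** With an assumed SD of 4 mmol/L at each time, the SE of the arm difference is 4√(2/25) = 1.13 for the 24-hour value alone. For change it is that value times √[2(1 − r)], where r is the correlation between pre-dose and 24-hour sodium: 1.34 at r = 0.3, 1.13 at r = 0.5 and 0.88 at r = 0.7. Change is thus not always more precise. Its value here is that it isolates what happened after dosing and registers a further fall in a patient who was already low, which neither status nor new onset does.

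**The case against.** **The placebo arm already deals with this.** Largely true. Pre-existing low sodium is balanced in expectation, so a reader who infers that the drug's effect cannot be seen, or that the comparison is biased between arms, goes too far. What remains is dilution by the fraction b and extra noise.

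**Hyponatraemia is also caught elsewhere.** It is a safety outcome event reported to day 90, and adverse events receive masked causality review. It would be wrong to say that the trial's whole view of hyponatraemia is one 24-hour status. But neither route, as described, states a pre-dose value or defines new onset, and adjudicators need the earlier value to tell onset from persistence.

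**The baseline sentence is not exhaustive.** Correct. It omits systolic blood pressure and time since onset, which minimisation needs, and the Glasgow coma scale, which eligibility needs. Factor VIII and VWF are assessed as change although no pre-dose draw is listed there. The data collection forms and full protocol are not shown. A reader might infer that no pre-dose sodium is collected at all; the article does not support that. It shows only that none is stated.

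**Definitions belong in the SAP.** A threshold may. Here, however, the article itself fixes the outcome as status at 24 hours, and collecting a baseline sodium would not by itself turn that into new onset or change.

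**Little depends on it.** The summaries are descriptive, the primary outcomes and the progression decision do not use sodium, and precision stays poor after the fix (SE 8.9 points on an 18-point difference in the example). This stands and limits the weight of the point.

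**Conclusion.** The point holds in a limited form. As worded, the 24-hour rate combines pre-existing and new hyponatraemia, and the article states neither a pre-dose value nor a definition that would separate them. The comparison of arms remains fair. If 5% to 20% of patients are low before dosing and stay low, the risk difference shrinks by 5% to 20%. In the worked example at 10%, the difference falls from 18 to 16.2 points and the SE is 11.1 rather than 8.9 points. The prevalences and new-onset rates are assumptions; only the 25 per arm comes from the article. This is a cheap improvement to a safety summary and not a flaw that threatens the feasibility aims.

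**What to change.** - Record the last sodium before dosing from the routine admission blood result. If the case report form already collects it, use that value.
- Define the main summary as new-onset hyponatraemia at 24 hours, meaning present then and absent before dosing, with the same threshold at both times.
- Report change in sodium (mmol/L) with a 95% CI by treatment received, as for the other safety data. An interval used for description fits the decision to make no formal comparison.
- List 24-hour prevalence separately, so that the outcome as now worded is still reported.
- Give the number of participants without a pre-dose value in each arm.

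The cost is one extra data field and a few lines in the SAP. The downside is that a few participants may lack a pre-dose result and drop out of the new-onset and change summaries; they remain in the prevalence listing.
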